## Methods and design

### Study design and objectives

ICECREAM is a randomised, open-label, phase II study of cetuximab monotherapy versus the combination of cetuximab and irinotecan. The primary objective is to determine the 6-month progression free survival (PFS) benefit of cetuximab alone or in combination with irinotecan in patients with *KRAS, NRAS, BRAF* and *PIK3CKA* wild type mCRC or *KRAS* G13D mutated mCRC. PFS is defined as the time from randomisation to disease progression according to RECIST criteria, version 1.1 [18]. Secondary objectives are to determine the response rate (as complete or partial responses according to RECIST criteria, version 1.1) in patients with “quadruple wild type” or *KRAS* G13D mutated mCRC. Overall survival benefit in the two patient cohorts will be determined based on death from any cause. The study will evaluate quality of life with FACT-C (Functional Assessment of Cancer Therapy), DLQI (Dermatology Quality of Life Index Questionnaire), and FACT-EGFRI 18 (Functional Assessment of Cancer Therapy, pertaining specifically to Epidermal Growth Factor Receptor Inhibition).

Tertiary and correlative objectives are to undertake exploratory studies of biological markers as predictors of outcome. Early tumour response will be measured by assessment of tumour shrinkage on CT imaging performed at 6 weeks post first treatment, based on independent review of volumetric tumour size.

Biological substudies aim to improve understanding of the mechanisms of cetuximab and any interaction with irinotecan in wild type and G13D mutated tumours. Since the identification of new biomarkers correlating with disease activity, and the efficacy and safety of treatments are rapidly evolving, a definitive list of biomarker studies remains to be determined at the time of these studies.

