### Statistical methods

The sample size of 100 patients is comprised of 50 patients with confirmed “quadruple wild type” status and 50 patients with a confirmed G13D tumour mutation. An intention to treat analysis will be undertaken, with the inclusion of all randomised patients.

In keeping with the randomized phase II study design, PFS was selected as the appropriate primary endpoint as this would not be influenced by subsequent cross over from monotherapy to combination treatment, which may occur at progression on study. Statistical assumptions were on the basis of retrospective data (Table 1) with a median PFS of 1.8 months in the cetuximab-alone arm versus 4.0 months for patients with KRAS G13D–mutated tumors receiving any cetuximab therapy [11]. This corresponds to a 6-month PFS rate of approximately 10 % for the monotherapy group and 35 % for the combination group. The G13D component of the study planned to recruit 25 patients per arm to match the wild-type cohort. This enabled 80 % power (α = .05) to detect an improvement from 15 to 40 % in 6-month PFS by using the Simon design for phase II trials. This magnitude of effect was chosen because we were interested in detecting a similar degree of benefit in the KRAS G13D–mutation population that was anticipated to be practice changing in patients with wild-type tumors. PFS and OS treatment effects were described by using hazard ratios (HRs) that were estimated by using Cox proportional hazards models. Completeness of the PFS was estimated by using a published equation [19]. Waterfall plots were constructed by using the biggest decrease compared with baseline in the sum of the target lesions. Patients with a decreased sum of target lesions but with new non-target lesions were set to a zero change but still qualified as having progressive disease. QoL changes over time were modeled by using generalized estimating equations. Analyses used SAS v9.3 (SAS Institute, Cary, NC).

**Table 1 Tab1:** Summary of current clinical trial PFS data on which statistical calculations are based

	KRAS unknown	KRAS WT	KRAS mutant	KRAS G13D
BOND study [1] cetuximab alone vs cetuximab + irinotecan	6 m PFS = 8 % vs. 30 %	NA	NA	NA
CO.17 [4] cetuximab vs best supportive care	N/A	6 m PFS cetuximab = 30 %	6 m PFS < 5 %	
De Roock [11] cetuximab vs no cetuximab	N/A	Median PFS 4.2 m vs 1.9 m	Median PFS 1.9 m vs 1.8 m	Median PFS 4.0 m vs 1.7 m

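### The 80% power quoted for 15% versus 40% belongs to a single-arm Simon test of the combination arm; the randomised monotherapy-versus-combination comparison at 25 per arm does not have it on 6-month PFS

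*Protocol article*

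**What the plan says.** Under Study design and objectives the article presents a comparison of arms: "ICECREAM is a randomised, open-label, phase II study of cetuximab monotherapy versus the combination of cetuximab and irinotecan". The Abstract names the 6-month PFS benefit as the primary endpoint, and allocation is 1:1 within genotype strata.

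Statistical methods converts retrospective medians of 1.8 and 4.0 months into 6-month rates of "approximately 10 % for the monotherapy group and 35 % for the combination group". It sets the G13D cohort at 25 patients per arm and continues: "This enabled 80 % power (α = .05) to detect an improvement from 15 to 40" per cent, "in 6-month PFS by using the Simon design for phase II trials". The sidedness of alpha is not given, and no other power figure appears. PFS and OS treatment effects are to be described with Cox hazard ratios.

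Planned futility analysis says a Simon two-stage design was applied to the G13D patients because the activity of the combination is of particular interest there. Futility is declared if all of the first seven combination patients have progressed.

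**The concern.** Read in order, the text gives a rate for each arm, a number per arm and then a power to detect an improvement. A reader will take 80% as the power of the monotherapy-versus-combination comparison. A Simon design tests one group against a fixed rate, and the concurrent control does not enter it.

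Two misreadings follow. A null comparison of the arms would be taken as coming from an 80%-powered trial. A positive Simon result in the combination arm might be taken as evidence of what irinotecan adds, which it cannot show. The Summary says the results will inform the need for phase III studies, so both misreadings matter.

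**Working it through.** **Inputs.** From Statistical methods: p0 = 0.15, p1 = 0.40, alpha = 0.05, 25 per arm in the G13D cohort. From Planned futility analysis: first stage n1 = 7 combination patients, stop at 0/7. Assumed here: no dropout; both sidednesses shown; exponential PFS for the hazard-ratio calculation.

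**1. Reproducing the 80%.** In a single-arm two-stage design with N = 25, let X1 be the number progression-free at 6 months among the first 7 and X2 the number among the next 18. The probability of a positive result is the sum, over first-stage counts that continue, of P(X1 = x) × P(X2 ≥ c − x), evaluated at p0 for alpha and at p1 for power. The optimal Simon design for these inputs has n1 = 7 and N = 25, stops at ≤1/7 and succeeds at ≥7/25. Its exact one-sided alpha is 0.049 and its power 80.6%. This matches both the 25 per arm and the seven first-stage patients, so the source of the 80% is clear.

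**2. Same design with the futility rule as printed (stop only at 0/7).** The article gives no final success boundary, so two are shown.

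| Success at | One-sided alpha | Power |
|---|---|---|
| ≥7/25 | 0.066 | 90.9% |
| ≥8/25 | 0.025 | 83.4% |

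Neither gives the 0.049 and 80.6% pair from step 1.

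**3. Randomised comparison of 6-month proportions, 25 versus 25, 15% versus 40%.** With the pooled normal formula, the mean rate is 0.275. The null SE is √(2 × 0.275 × 0.725/25) = 0.1263. The alternative SE is √(0.15 × 0.85/25 + 0.40 × 0.60/25) = 0.1212.
- Two-sided: Φ((0.25 − 1.96 × 0.1263)/0.1212) = 50.8%.
- One-sided: Φ((0.25 − 1.645 × 0.1263)/0.1212) = 63.6%.

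Exact enumeration over two Binomial(25) arms gives:

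| Test | Two-sided 0.05 | One-sided 0.05 |
|---|---|---|
| Fisher | 38.3% | 53.2% |
| Pearson chi-square | 53.2% | 64.4% |

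With the article's other rate pair, 10% versus 35%, the Fisher–Pearson ranges are 45–60% two-sided and 60–71% one-sided. Without continuity correction, 80% power for 15% versus 40% needs 49 per arm two-sided or 39 one-sided.

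**4. Log-rank or Cox comparison.** Under exponential PFS, HR = ln 0.40 / ln 0.15 = 0.483, so |ln HR| = 0.728. By Schoenfeld's formula, power = Φ(√D/2 × 0.728 − z), where D is the number of events in the cohort.

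| Events D | Two-sided 0.05 | One-sided 0.05 |
|---|---|---|
| 45 | 68.5% | 78.7% |
| 50 | 73.0% | 82.3% |

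Two-sided 80% needs 60 events, more than the 50 patients in a cohort.

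**5. Precision.** The 95% CI half-width for the 6-month difference is 1.96 × 0.1212 = 0.24, or about 24 percentage points.

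**The case against.** - **The article names the Simon design in the same sentence as the 80%, and the futility section ties that design to the combination.** True, and the arithmetic behind it is sound. But nowhere does the article say that the 80% concerns one arm against a fixed 15%, and the surrounding sentences describe two arms. Non-comparative randomised phase II arms are legitimate when declared; here the objective is worded as one regimen versus the other.
- **A reader might infer that the randomised comparison has only 40–50% power, little better than a coin toss.** The article does not support that as a general statement. It holds only for a two-sided test of 6-month proportions. Sidedness is unstated, the Simon alpha being reproduced is one-sided, and the only between-arm model named is Cox, which does better (step 4). With the stated medians, HR = 1.8/4.0 = 0.45, and the same formula with 45–50 events gives 76–81% two-sided and 85–88% one-sided. Even so, the power sentence is about 15% to 40% in the 6-month rate. On that effect no test of proportions at 25 per arm and alpha 0.05 reaches 80%, and Cox does so only one-sided with nearly every patient having an event.
- **Pooling the cohorts (50 per arm) would give about 74–82% two-sided.** But the article attaches the power claim to the G13D component alone.
- **The choice of between-arm test belongs in the full protocol or SAP.** Agreed. Its absence from the article is no fault. The point is a stated power attached to the wrong contrast.
- **The 0/7 rule might be thought to invalidate the design's power.** It does not. With success at ≥8/25, power is still above 80% and alpha below 0.05. The printed figures simply do not correspond to the printed rule under either boundary checked.

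**Conclusion.** The power statement is wrong as written. It is a mismatch between design and claim, not an arithmetic slip. The 80% is the power of a one-sided, single-arm test of the combination against a fixed 15%. For the randomised comparison within a cohort, at 15% versus 40%, power is about 38–53% two-sided and 53–64% one-sided on the 6-month proportion. On a log-rank or Cox comparison it is about 68–73% and 79–82% respectively.

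The proportion figures assume no dropout and analysis within one cohort. The hazard-ratio figures also assume exponential PFS and 45–50 events among 50 patients. That the comparison of 6-month proportions falls short of 80% at alpha 0.05 does not depend on the sidedness or on which of the article's two rate pairs is used; the size of the shortfall does.

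**What to change.** 1. Reword the power sentence so that the 80% refers to the combination arm of the G13D cohort, tested one-sided against a fixed 6-month PFS rate of 15%, with 40% as the alternative.
2. Add the between-arm power within a cohort, naming test and sidedness: 38–53% two-sided and 53–64% one-sided on the 6-month proportion; about 68–73% and 79–82% by log-rank or Cox, with the assumptions given.
3. Say that the monotherapy-versus-combination comparison is not powered at 80% on 6-month PFS and will be reported as an estimate with a 95% CI, expected half-width about 24 percentage points on the 6-month difference.
4. Reconcile the quoted alpha and power with Planned futility analysis. The design that gives 80.6% stops at ≤1/7, while that section stops only at 0/7. State the final success boundary and the exact alpha and power of whichever rule applies.

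The cost is wording only. The stated power becomes less favourable; no extra patients are needed.

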### Planned futility analysis

As the activity of the combination is of particular interest in patients with G13D KRAS mutated tumours, Simon’s II stage design was applied to this group of patients. Futility will be declared if in the first seven eligible patients having at least six months of combination treatment, all seven patients have progressed.

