### Pre-trial screening procedures and randomisation and stratification

Entry into the study is conditional on confirmation of tumour genotype by means of mutation analysis of representative samples of diagnostic tumour tissue. *KRAS* G13D status is determined by local pathology laboratories, whereas “quadruple wild type” status is determined by a central reference laboratory, the Centre for Translational Pathology, Melbourne, Australia. Archival tumour samples from the primary colorectal cancer or any metastatic site are acceptable for mutation analysis. All specimens are received as formalin fixed, paraffin embedded tissue biopsy blocks (FFPE), which upon arrival are cut into 10 μm sections by microtome and transferred onto glass slides before de-waxing and DNA extraction. An additional 4 μm slide section is stained with haematoxylin and eosin, examined by a pathologist to determine and mark the region of tumour, and then used to determine the areas of tumour to be macrodissected from unstained slides. DNA is extracted using Qiagen FFPE DNA extraction kits and successful DNA extraction is confirmed by Qubit DNA quantitation and LabChipGX DNA fragmentation assessment. For Sanger sequencing, targeted regions of interest from exon 15 of the BRAF gene, exons 9 and 20 of the PIK3CA gene, and exons 2, 3, and 4 of both KRAS and NRAS genes are amplified separately by PCR and sequenced using BigDye terminator chemistry on an ABI 3730 genetic analyser. Mutation analysis uses Mutation Surveyor software. For next generation sequencing (NGS) analysis, targeted regions of interest from exon 15 of the BRAF gene, exons 9 and 20 of the PIK3CA gene, and exons 2, 3, and 4 of both KRAS and NRAS genes are amplified and linked to barcoded NGS adapters with a two-step multiplex PCR protocol. The resulting library is sequenced on an Illumina MiSeq next generation sequencer. Mutations are detected with MiSeq Reporter software.

Written informed consent must be obtained, and patients must be randomised before starting the study treatment and planned to start within 14 days of randomisation.

Patients are centrally randomised in a 1:1 ratio and be stratified according to “quadruple wild type” or *KRAS* G13D mutational status, and treating hospital. This publication represents the current protocol version (V4).

The ICECREAM trial opened in November 2012 with a recruitment period of two years.

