### Administration of study treatment

Patient will be randomised to one of two treatment arms:*Arm A*Cetuximab monotherapy (Cetuximab 400 mg/m^2^ IVI on Day 1, followed by 250 mg/m^2^ IVI every week).*Arm B*Cetuximab and irinotecan combination therapy (Cetuximab 400 mg/m2 IVI on Day 1, followed by 250 mg/m2 IVI every week; Irinotecan 180 mg/m^2^ IVI on Day 1 after cetuximab infusion, then every 14 days).

Body surface area (BSA) will be calculated using actual body weight. Irinotecan dose is capped at that for BSA 2.2 m^2^; and no dose capping is stipulated for cetuximab.

The starting dose of irinotecan is at the discretion of the investigator, taking into account prior irinotecan dosing and adjustments. Whilst on study, all patients will be permitted a maximum of two further reductions in irinotecan (level 1 of −20 % and level 2 of −40 %), excluding dose reductions at commencement. Cetuximab dose reductions are permitted beyond level 2 (dose level 3 of 100 mg/m^2^, and dose level 4 of 50 mg/m^2^). Treatment will continue until disease progression, unacceptable toxicity, or patient or physician request for cessation.

In Australia, for patients with *KRAS* WT colorectal cancer, cetuximab and irinotecan are approved treatments and will be supplied through the Pharmaceutical Benefits Scheme (PBS) and available through local hospital supply. For Australian patients with *KRAS* G13D mutant colorectal cancer, cetuximab will be supplied by Merck Serono Australia Pty Ltd.

In England, Italy and Spain only patients with the G13D tumour mutation will be recruited and cetuximab is supplied by Merck Serono Australia Pty Ltd. The Belgian site will recruit patients with “*KRAS* quad wild type” tumour status and the study treatments are approved for use and sourced as per local hospital supply.

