### Treatment discontinuation

Study treatment will be permanently discontinued for documented progressive disease as per RECIST 1.1; unacceptable toxicity (as determined by the patient or treating clinician); delay of treatment for more than 28 days due to treatment-related adverse events; if the treating clinician determines that continuation of treatment is not in the patient’s best interest; for occurrence of an exclusion criterion affecting patient safety, e.g. pregnancy or psychiatric illness; failure to comply with the protocol, e.g. repeatedly failing to attend scheduled assessments, or if the patient withdraws their consent to participate in the study. Treatment after discontinuation of study treatment will be at the discretion of the patient’s clinician.

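### As worded, the G13D futility rule draws its seven patients from those who stayed on combination treatment for six months, which leaves out the early progressors it needs to count

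*Protocol article*

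**What the plan says.** Under Planned futility analysis, the article states that "Simon’s II stage design was applied to this group of patients", meaning those with G13D tumours. The look uses the "first seven eligible patients having at least six months of combination treatment", and futility is declared if "all seven patients have progressed". The rule gives no time by which progression must have occurred.

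Two other sections fix how long treatment lasts. Administration of study treatment: "Treatment will continue until disease progression, unacceptable toxicity, or patient or physician request for cessation". Treatment discontinuation: "Study treatment will be permanently discontinued for documented progressive disease as per RECIST 1.1".

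Two more fix the clock. Study design and objectives: "PFS is defined as the time from randomisation to disease progression according to RECIST criteria, version 1.1". The section on screening, randomisation and stratification: "patients must be randomised before starting the study treatment and planned to start within 14 days of randomisation".

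Statistical methods gives the G13D planning figures: 25 patients per arm, 80% power, α = .05, and an improvement in 6-month PFS from 15% to 40% under a Simon design.

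**The concern.** A first-stage futility look should take the first few patients treated and count how many reach the endpoint. Here, entry to the set of seven depends on six months of combination treatment, and treatment ends at progression. Entry therefore depends on the outcome that the look is meant to test.

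Three groups randomised to the combination drop out of the count: those who progress early, those who die early, and those who stop irinotecan before six months. The last group arises by rule, because the dose modification section has patients whose irinotecan is delayed 28 days or more cease it and go on with cetuximab alone.

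The outcome has the opposite problem. A patient who progresses in month 8 met the 6-month endpoint, yet counts towards futility.

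At stake is whether the look happens when it is needed. Followed literally, it would seldom take place if the combination is inactive and would usually take place if it is active.

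**Working it through.** **1. The plan's own figure.** I searched exact two-stage Simon designs with p0 = 0.15, p1 = 0.40, α = 0.05 and power 0.80. The article does not state sidedness; I assumed one-sided, the Simon convention. The optimal design has 7 patients in stage 1 and 25 in total. It stops at 1 or fewer successes in 7 and needs more than 6 successes in 25. Its exact α is 0.0491 and its power 0.8056. The article's 25 per arm and its first seven patients both reproduce, so the seven are recognisably a Simon first stage.

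**2. Who can qualify on the literal wording.** For a patient randomised to Arm B:
- PFS starts at randomisation, and treatment starts after it.
- Treatment stops permanently at documented progression.
- So six months of combination treatment implies no documented progression for at least about six months from randomisation.

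The number who qualify is therefore at most the number progression-free at six months. Stops for toxicity or by request lower it further, so the figures in step 3 are upper bounds.

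**3. Chance that seven ever qualify.** Let X be the number qualifying among 25, with X ~ Binomial(25, p) at most, where p is true 6-month PFS.

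P(X ≥ 7) = 1 − Σ C(25,k) p^k (1−p)^(25−k), summed over k = 0 to 6.

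| True 6-month PFS | Expected number, 25 × p | P(X ≥ 7) |
|---|---|---|
| 10% | 2.5 | 0.0095 |
| 15% | 3.75 | 0.0695 |
| 35% | 8.75 | 0.8266 |
| 40% | 10 | 0.9264 |

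The 15% and 40% are the article's design rates. The 10% and 35% are its approximate 6-month rates for monotherapy and combination from retrospective data.

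**4. What the rule can then see.** Among Arm B patients who qualify, none can have documented progression before completing six months of treatment. The rule can fire only on progression found at about six months or later.

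**5. The same boundary with the seven defined by follow-up.** Take the first seven G13D patients randomised to the combination, each with six months of follow-up whatever their treatment duration. The written boundary, no successes in seven, stops with probability (1 − p)^7:
- p = 0.10: 0.90^7 = 0.478
- p = 0.15: 0.85^7 = 0.321
- p = 0.35: 0.65^7 = 0.049
- p = 0.40: 0.60^7 = 0.028

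This is the behaviour that the literal wording loses.

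**The case against.** The strongest reply is that the literal reading is not what was meant. The seven match the first stage of the Simon design behind n = 25, and the natural purpose of six months is to let the endpoint mature. If the phrase means six months since starting the combination, the look takes place and the percentages in step 3 do not apply. I accept that as the probable intention. However, nothing in the article turns treatment into follow-up, and a stopping rule has to work as worded.

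A second reply is that a condensed article leaves evaluability detail to the full protocol. That is fair for handling rules that are not mentioned. It does not cover an inclusion condition that the article does state and that conflicts with its own treatment rules.

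A reader might also infer more than the documents support:
- **That the rule cannot detect futility, or that the G13D cohort has no futility protection by design.** The rule can still fire on later progression, and the underlying design is sound if follow-up was meant.
- **That the set contains only 6-month successes.** Statistical methods allows patients on monotherapy to cross over to the combination at progression. Such a patient could have six months of combination treatment after failing the endpoint. The statement holds for patients randomised to Arm B, the natural reading, but the rule does not say so.
- **That the rule breaches the intention-to-treat commitment.** The sentence "An intention to treat analysis will be undertaken, with the inclusion of all randomised patients" governs the main analysis. A first-stage look at seven patients in one arm of one cohort is necessarily a subset.

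**Conclusion.** The concern holds as a defect in how the futility set is defined. As worded, among patients randomised to Arm B, the rule excludes early progressors, selects patients progression-free at about six months, and could declare futility on patients who met the 6-month endpoint.

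On the literal reading, with 25 combination patients, seven would ever qualify with probability at most 7.0% at a true 6-month PFS of 15% (1.0% at 10%), against at most 92.6% at 40%. If six months of follow-up was intended, the written boundary works in the right direction: 0.321 at 15% and 0.028 at 40%.

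The figures assume independent patients and 25 randomised to the combination; those for the literal reading also treat six months on treatment as no more common than being progression-free at six months. The sample size is not in question here, and the PFS and overall survival comparisons do not depend on this sentence.

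**What to change.** Replace the condition in "first seven eligible patients having at least six months of combination treatment" with a set defined by randomisation and follow-up:
- **Set:** the first seven eligible G13D patients randomised to Arm B, each followed for six months from randomisation or to an earlier event, regardless of treatment duration. This also keeps crossover patients out.
- **Outcome:** failure is progression or death by six months; success is being alive and progression-free at six months. Death needs naming because the article's PFS definition mentions only progression.
- **Delete** the requirement for six months of combination treatment.

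The cost is a rewording of the rule, with no added patients, visits or data.

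The rewording leaves the boundary as it is. The Simon optimal design in step 1 stops at 1 or fewer successes in seven (probability 0.717 at 15% and 0.159 at 40%), whereas the article stops only at none. That is a separate question, which the sponsor can settle in the same edit by stating the intended boundary and the final cut-off.

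### The stage-1 futility boundary (0 of 7) is not that of the Simon optimal design which reproduces the plan's 7, 25 and 80% power (1 or fewer of 7); the two sections need reconciling

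*Protocol article*

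**What the plan says.** Protocol article, Statistical methods: the G13D component "planned to recruit 25 patients per arm to match the wild-type cohort". The next sentence gives the operating characteristics, "This enabled 80 % power (α = .05"), and the effect and method: "to detect an improvement from 15 to 40 % in 6-month PFS by using the Simon design for phase II trials". The same paragraph also translates retrospective medians into a "6-month PFS rate of approximately 10 % for the monotherapy group and 35 % for the combination group", but the power statement uses 15% and 40%.

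Protocol article, Planned futility analysis: "Simon’s II stage design was applied to this group of patients", meaning the G13D patients. Futility is assessed "in the first seven eligible patients having at least six months of combination treatment" and is declared if "all seven patients have progressed". Counting a success as a patient progression-free at six months, the rule stops at 0 of 7 and continues at 1 or more of 7. The article gives no final-stage cut-off.

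**The concern.** A Simon two-stage design is a set of four linked numbers: first-stage size, first-stage boundary, total size and final cut-off. Alpha and power belong to the set, so one number cannot be altered while the others keep their meaning. The article gives two sizes (7 and 25), a power and an alpha that all agree with one well-defined design, the optimal one for 15% versus 40%. Its first-stage boundary does not belong to that design.

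Two things are at stake. The first is how much protection the futility look gives: a laxer boundary lets an inactive combination run to full accrual more often. The second is the final decision. Anyone who looks up the optimal design to supply the unprinted cut-off, and applies it after the printed boundary, would test at an alpha above the stated one.

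**Working it through.** **Inputs.** From Statistical methods: p0 = 0.15, p1 = 0.40, alpha = 0.05, power = 0.80, n = 25 in the arm tested. From Planned futility analysis: n1 = 7, stage-1 boundary r1 = 0. Assumption: alpha is one-sided, which is usual for a Simon design; the article does not give sidedness.

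**Formulas.** Stop after stage 1 if X1 ≤ r1, with X1 ~ Bin(n1, p); succeed if the total exceeds r.

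- Probability of early stopping: PET(p) = P(X1 ≤ r1).
- Probability of declaring success: sum over x > r1 of P(X1 = x) · P(X2 ≥ r + 1 − x), with X2 ~ Bin(n − n1, p). This is alpha at p0 and power at p1.
- Expected size under p0: n1 + (1 − PET(p0)) · (n − n1).

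**Step 1: reproduce the plan's figure.** An exact search over two-stage designs with n up to 36, at the stated rates, alpha and power, gives:

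- Optimal (smallest expected size under p0): r1/n1 = 1/7, r/n = 6/25. Stop at 1 or fewer of 7; succeed at 7 or more of 25. Alpha 0.0491, power 0.8056.
- Minimax (smallest total): 1/9, 5/19.

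The optimal design gives the plan's 7, 25 and 80% together. Neither design stops only at 0 of 7.

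**Step 2: early stopping at a true 15%.**

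- Printed rule: 0.85^7 = 0.321.
- Optimal rule: 0.85^7 + 7 × 0.15 × 0.85^6 = 0.321 + 0.396 = 0.717.
- Expected size, optimal: 7 + (1 − 0.7166) × 18 = 12.1.
- Expected size, printed, with n = 25: 7 + (1 − 0.3206) × 18 = 19.2.

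**Step 3: early stopping at a true 40%.**

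- Printed rule: 0.60^7 = 0.028.
- Optimal rule: 0.60^7 + 7 × 0.40 × 0.60^6 = 0.028 + 0.131 = 0.159. This loss is already inside the 0.806 power.

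**Step 4: alpha and power by boundary and final cut-off (n = 25).**

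| Stop at stage 1 if | Succeed if | Alpha (15%) | Power (40%) | PET at 15% | Expected n at 15% |
|---|---|---|---|---|---|
| 1 or fewer of 7 | ≥ 7 of 25 | 0.049 | 0.806 | 0.717 | 12.1 |
| 0 of 7 | ≥ 7 of 25 | 0.066 | 0.909 | 0.321 | 19.2 |
| 0 of 7 | ≥ 8 of 25 | 0.025 | 0.834 | 0.321 | 19.2 |

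The second row differs from the first by the path that the printed rule keeps open. One success in 7 (0.396), followed by at least 6 of the next 18 (0.0419), adds 0.396 × 0.0419 = 0.0166, and 0.0491 + 0.0166 = 0.0657.

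**Step 5: variants.** None of these has a 0-of-7 boundary (all at 80% power):

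- 10% versus 35%, alpha 0.05: optimal 1/8, 4/22; minimax 1/11, 4/18.
- 15% versus 40%, alpha 0.025: 2/10, 8/31 and 2/14, 7/24.
- 15% versus 40%, alpha 0.10: 1/7, 4/18 and 1/9, 4/16.

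Nor is the 80% a two-arm figure: comparing 15% with 40% at 25 per arm has about 51% power two-sided and 64% one-sided.

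**The case against.** The strongest reply is that no stated operating characteristic is shown to be false. Stopping at 0 of 7 and requiring at least 8 of 25 gives alpha 0.0246 and power 0.834, within the stated 0.05 and 80%. The article never calls its design optimal, and it quotes no stopping probability or expected size. This stands: 0 of 7 is a legitimate two-stage rule, though not the Simon optimal or minimax one.

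A reader might infer that the trial's type I error exceeds 0.05. The documents do not support that. The 0.066 needs a final cut-off of 7 of 25, which comes from the optimal design and is printed nowhere; an article may leave the cut-off to the full protocol or SAP.

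A reader might also infer that 0 of 7 is a slip for 1 of 7. That is not established either. The article says 25 was chosen to match the wild-type cohort. A zero boundary also has a possible rationale in the plan's own 35% for the combination: 0.65^6 = 7.5% and 0.65^7 = 4.9%, so seven is the smallest group in which no success has less than 5% probability at that rate. Against this, a 0-of-7 rule already meets the stated alpha and power at 22 patients (at least 7 of 22: alpha 0.036, power 0.831). It therefore does not need 25, whereas the optimal design gives exactly 25. The joint match remains strong but circumstantial evidence.

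Finally, a laxer look lowers the risk of abandoning an active combination: 2.8% against 15.9% at a true 40%. That is a fair trade-off in a rare subgroup, but it should be a visible choice.

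**Conclusion.** The point holds as an inconsistency between two sections. The sizes and power in Statistical methods are those of the Simon optimal design for 15% versus 40%, whose first-stage boundary is 1 or fewer of 7; Planned futility analysis prints 0 of 7. With the total at 25, the printed boundary cuts the chance of stopping an inactive combination from 72% to 32% and adds about seven patients to the expected size (19.2 − 12.1 = 7.1), whatever the final cut-off. The effect on type I error is conditional: 0.066 with a cut-off of 7 of 25, 0.025 with 8 of 25.

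This rests on one-sided alpha, on exact binomial calculation with six-month status known for every patient counted, and on reading the named Simon design as the optimal one. Severity is moderate: a stated decision threshold is affected, but a valid reading of the printed rule exists and the documents do not settle which boundary was intended.

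**What to change.** Reconcile Planned futility analysis with the Simon design behind the power statement, and print the boundaries for both stages. Either of two statements would be consistent:

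- If the optimal design was used, state 1/7 and 6/25: futility at 1 or fewer of 7, success at 7 or more of 25; alpha 0.049, power 0.806, 72% stopping probability at 15%.
- If 0 of 7 is deliberate, say that it is not the optimal Simon design, pair it with a final cut-off of at least 8 of 25, and report alpha 0.025, power 0.83 and 32% stopping probability at 15%.

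The sponsor has to say which applies. In both cases, state that alpha is one-sided if that is meant. The cost is wording only, with no change to the planned 25 per arm. Under the first statement, the chance of stopping at stage 1 when the true rate is 40% is 15.9%, already counted in the power. Under the second, an inactive combination would run to 25 patients about two times in three (1 − 0.32 = 0.68).
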